#### Property Attributions task: Assessing the role of folk physics, biology, psychology, and sociology in reasoning about religious agents

The Property Attributions task is designed to evaluate conceptualizations of religious and supernatural agents [for similar tasks, see 8,38,55]. This is part of the Child Protocol; see Fig 2.

*Task design and procedure*. The Property Attributions task consists of a 20-item close-ended battery intended to assess participants’ representations of the physical, biological, cognitive-epistemic, social-emotional, and sociological properties and constraints of two to three religious/supernatural agents, as compared to the properties and constraints of ordinary human agents.

The task features the “Biggest” god [51] in the cultural-religious setting as well as 1–2 additional prominent religious agents. These religious/supernatural agents are also featured in the Sorting task (described in the previous section) and in the Justifications task (described in a later section); if a child indicates that they are not familiar with one of these agents in the Sorting Task, this agent is omitted from the Property Attributions and Justifications tasks for that child. Questions about human or human-like prophets and other agents who are not the “Biggest” god are referred to as “Agent 1” for the purposes of this task, and always precede questions about the “Biggest” god (“Agent 2”). Throughout the task, these religious/supernatural agents are compared to an ordinary human (“a person”). See Table 2 for items selected for each US sample.

**Table 2 pone.0292755.t002:** Sample-specific item selection for the Property Attributions and Justifications tasks, for the five religions included in US samples.

	Religion				
Agent	*Protestantism*	*Catholicism*	*Church of Jesus Christ of L*.*D*.*S*.	*Judaism*	*Islam*
*1*	Jesus	Jesus	Jesus	Elijah	the Prophet Muhammad
*2*	God	God	God	God^a^	Allah
*3*	the Holy Spirit	the Holy Spirit	the Holy Spirit	Jesus	Jesus

Unaffiliated children in the US are shown the version of the protocol that corresponds to the religion with which they are likely most familiar (see main text for details). See main text for descriptions of network-wide guidelines for item selection. “L.D.S.” stands for “Latter-day Saints.”

^a^ If the researcher becomes aware that the child is more familiar with the term “Hashem” or “Adonai” then the more familiar term is used in place of “God” throughout the Child Protocol.

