We also expect that children’s responses to religious vs. neutral properties will vary across domains (e.g., that the difference between ascriptions of religious vs. neutral beliefs might function as a more powerful indicator of religious group membership than the difference between behaviors related to religious vs. neutral holidays) [see 64, 65]. To test this hypothesis, we will examine statistical interactions between property type (religious vs. neutral) and indicator type (belief, holiday, prayer-like practice) on children’s responses in the second block of the task.

Developmentally, we hypothesize that children’s tendency to recognize religious indicators and infer religious group membership will increase with age [65–67]. To test this hypothesis, we will examine a statistical interaction between property type (religious vs. neutral) and participant age (4–10 years) on children’s responses in the second block of this task.

We will conduct a parallel set of analyses for data from the first block of this task, in which children are asked to judge how similar the characters are to themselves (“Is [she/he] like you or different from you?”). These analyses will assess whether children judge characters associated with religious vs. neutral properties to be more similar to themselves, and whether this tendency differs across specific religious indicator types (belief, holiday, prayer-like practice) or across the age range of our samples. These analyses will be exploratory; we do not have strong predictions about the strength or direction of these results.

Beyond this, we plan to examine higher-order statistical interactions (e.g., an interaction between property type, indicator type, and participant age); to conduct within-subjects analyses of the relationships between children’s responses in the first and second blocks of this task (i.e., between children’s similarity judgments and their recognition of religious indicators); to compare responses across samples from different cultural-religious groups; to explore relationships between children’s responses in this task and information provided in the Parent Survey; and to examine relationships between this and other tasks included in the Child Protocol.

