#### Justifications task: Assessing self-reported information sources for religious beliefs and behaviors

Building on previous work on children’s representations of supernatural phenomena, the Justifications task is designed to evaluate children’s understanding of their own “source knowledge” regarding the 2–3 religious agents featured in the Property Attributions task ([for similar tasks, see, e.g., 8, 38, 52, 53, 55, 84, 85]). This task is part of the Child Protocol; see Fig 2.

*Task design and procedure*. The Justifications task directly follows the Property Attributions task (described in an earlier section) and features the same set of agents included in that task—i.e., “normal, everyday people” as well 2–3 religious/supernatural agents (which we refer to in this manuscript as “Agent 1,” “Agent 2,” and, if applicable, “Agent 3”).

The task consists of a separate block of questions for each agent. Blocks are presented in a fixed order matching the order of presentation of agents in the Property Attributions task; as in that task, the first agent to be discussed is “people,” followed by Agent 1, Agent 2, and (if applicable) Agent 3.

Each block begins with a very brief introduction—“You just answered a lot of questions about [agent]”—followed by three open-ended questions presented in a fixed order: (1) “What else do you know about [agent]? You can tell me stories or any other things you know about [agent]”; (2) “Can you tell me more about how you know all of this about [agent]?”; and (3) “If you wanted to know more about [agent], how would you find out?”

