*Planned analyses*. Before describing our analysis plans, we note that analyses of the many open-ended questions included in this task will require the development of coding schemes to note the presence and extent of various kinds of content (e.g., identifying certain content as “religious”; counting mentions of “God” or other religious agents; coding different types of explanations) as well as various manners of speaking (e.g., noting the use of generic sentences). In particular, we anticipate adapting the coding scheme developed by Harris et al. [49] and further expanded by Davoodi et al. [53] to characterize different types of explanations that children might give over the course of this task, including elaborations (e.g., of causal processes or properties of the agent), discussions of the source of their knowledge (e.g., references to learning about the agent in school, from a family member, from a religious text), and references to encounters with the agent (e.g., recounting first- or second-hand personal experiences with the religious agent).

First, we hypothesize that, for all open-ended questions, older children will offer richer and more detailed examples, descriptions, and explanations of what they know and how they know it [see 53, 54, 86]. To test this hypothesis, we will examine the main effects of participant age (4–10 years) using any relevant coding schemes we have developed to quantify and characterize children’s responses. We also anticipate examining the main effects of agent (people, Agent 1, Agent 2, and, if applicable, Agent 3), as well as statistical interactions between agent and participant age.

In terms of children’s perceptions of community consensus, we hypothesize that children will perceive stronger community consensus when asked about a normal, everyday person than when asked about the two or three supernatural/religious agents, and that this difference will increase with age [see 53, 87]. To test these hypotheses, we will examine the main effect of agent as well as statistical interactions between agent and participant age, considering the question about community consensus alone.

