In terms of children’s source knowledge, we hypothesize that children will be more likely to name specific sources when asked about the two or three supernatural/religious agents than when asked about people; that mentions of specific sources will be inversely related to perceptions of community consensus (i.e., children will be more likely to name specific sources when discussing agents whose reality status they perceive to be controversial within their community); and that both of these effects will be exaggerated among older children [see 53]. To test these hypotheses, we will examine the main effect of agent, statistical interactions between agent and participant age, the main effect of community consensus, and statistical interactions between community consensus and participant age, considering the question about source knowledge alone.

Beyond these predictions, we plan to conduct exploratory analyses of all of the closed-ended questions that were not detailed in the current planned analyses; to compare responses across samples from different cultural-religious groups; to explore relationships between children’s responses in this task and information provided in the Parent Survey; and to examine relationships between this and other tasks included in the Child Protocol.

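### Justifications task: the main effect of community consensus does not separate the within-child relation, which the hypothesis describes, from differences between children

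*Protocol article*

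**What the plan says.** All places are in the protocol article. The main text is the Justifications task under Research question 3.

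- **Layout of the data.** "The task consists of a separate block of questions for each agent", and the order is fixed: "as in that task, the first agent to be discussed is “people,” followed by Agent 1, Agent 2, and (if applicable) Agent 3". Table 2 lists three religious agents for every US version, so the US design number is 1 + 3 = 4 blocks. The Property Attributions section adds that if a child does not know an agent, "this agent is omitted from the Property Attributions and Justifications tasks for that child". Both the source question and the consensus question are asked in each block.
- **Hypothesis.** Source mentions are expected to be inversely related to perceived consensus. This is explained as follows: "children will be more likely to name specific sources when discussing agents whose reality status they perceive to be controversial within their community". The effect is expected to be stronger in older children.
- **Test.** The sentence opens with the agent terms: "we will examine the main effect of agent, statistical interactions between agent and participant age, the main effect of community consensus". Its consensus part reads in full: "the main effect of community consensus, and statistical interactions between community consensus and participant age, considering the question about source knowledge alone". Nothing is said about separating within-child from between-child association, or about whether agent and consensus share one model.
- **Related prediction.** "children will perceive stronger community consensus when asked about a normal, everyday person than when asked about the two or three supernatural/religious agents". The article also expects more source naming for the religious agents than for people.

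**The concern.** Age varies only between children, and agent is set by the design. Consensus is different: it is the child's own answer, given once per block, so it varies both within and between children. Two questions are therefore possible. Does a given child name more sources for the agents that child sees as contested? Do children who generally see less agreement generally name more sources? The explanation of the hypothesis points to the first. The named test answers a blend of the two.

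What is at stake is the interpretation of a directional prediction. A trait of the child, such as a general readiness to elaborate or to report disagreement, could produce the predicted sign with no agent-level relation. A trait acting in the other direction could hide a real one. The consensus-by-age interaction inherits the same blend, because such traits may also change with age.

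**Working it through.** The article gives no error rate, power or effect size for this test, so there is no figure to reproduce. The check has an algebraic part and a simulated part.

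**1. Why a random intercept is not enough.** In the linear case with K blocks per child, the coefficient of an undivided predictor is

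b = λ·b_within + (1 − λ)·b_between, with λ = S_W / (S_W + φ·S_B) and φ = σ²_e / (σ²_e + K·σ²_child).

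S_W and S_B are the within- and between-child sums of squares of consensus, after any agent terms. Ordinary regression has φ = 1. A random intercept lowers φ, but not to zero. Only a split (or a conditional analysis) isolates b_within.

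**2. Simulation with agent in the model.**

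- From the article: four blocks per child; 75 children (planned US minimum per sample), 100 (planned maximum) and 600 (six US samples × 100).
- Assumed: consensus 95/75/75/65% and source naming 20/45/45/45% for people and Agents 1–3; child-level SD 1.2 on the logit scale; correlation rho between the child's consensus and source traits; true within-child effect zero.
- Analysis: logistic GEE, exchangeable, robust standard errors, two-sided 5%, with age, agent and agent-by-age.

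False-positive rates for the undivided consensus term (two values are separate runs):

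| rho | 75 children | 100 children | 600 children |
|---|---|---|---|
| 0 | 7% | 6% | 5% |
| −0.3 | 12%, 9% | 12%, 13.5% | 44% |
| −0.5 | 26%, 19% | 18%, 21.5% | 82%, 87% |

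A further run gave 4–5% or less at rho 0, and about 19–25% at 75–100 children for rho −0.5. The spread is simulation noise: with 300 replicates and a rate near 0.2, the Monte Carlo standard error is √(0.2 × 0.8 / 300) = 0.023. The rows for 75–100 children are best read as nominal, about 11–12%, and about 20–25%. The within-child deviation term rejected in about 2–8% of runs throughout. At rho −0.5 and 600 children the median odds ratio was 0.75 for the undivided term and 0.99 for the deviation term (truth 1).

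**3. Simulation with a random intercept.** This used a linear probability model with 75 children, 600 runs per cell, rejection only in the predicted direction (nominal 2.5%), and one trait fully shared by both answers, which is an extreme case.

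| Data contain | Consensus alone | + agent | Random intercept + agent | Within-child + agent |
|---|---|---|---|---|
| Neither effect | 1.8% | 2.5% | 2.7% | 3.2% |
| Agent differences only | 6.7% | 2.0% | 2.2% | 3.2% |
| Child trait only | 68% | 69% | 46% | 2.8% |
| Both | 86% | 77% | 51% | 3.2% |

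With the child trait only, the mean coefficient was −0.175 for consensus alone, −0.131 with random intercept and agent, and −0.006 within child. The random-intercept model keeps 0.131/0.175 = 75% of the spurious slope.

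**4. The agent route.** With agent differences only, false support at 450 children was 33.5% without agent in the model and 1.3% with it. Putting agent in the model closes this route; it does not close the child-trait route.

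**The case against.** The strongest reply is that the article names effects, not models. It calls these the most basic analyses of a largely exploratory protocol, and an article may leave clustering and centring to a fuller plan. That stands against any claim that the repeated blocks will be ignored. A reader might infer one pooled analysis over all blocks, but the text does not say so. It does not dispose of the point, because the article does name the quantity to be tested, and adding a random intercept later would not turn that quantity into the within-child relation.

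A reader might also infer that the contrast between people and religious agents will by itself produce the inverse relation. The article does predict that agent type moves consensus and source naming in opposite directions. But the sentence that names consensus also lists agent and agent-by-age for the same outcome, so a joint model is a natural reading. Under it this route is closed. What remains is that the joint model is not stated.

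Third, the main clause of the hypothesis is general, and a comparison between children who differ in perceived consensus also fits it. This stands: the between-child association is a legitimate result to report, not merely a nuisance.

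Fourth, nothing in the article supports a negative child-level correlation of any particular size. This also stands, and limits what can be said about magnitude.

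Finally, the Religious Indicators section plans "to conduct within-subjects analyses of the relationships between" the two blocks of that task. This shows that the article can name the within-child level, but it is an additional analysis of another task and does not amount to a contradiction.

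**Conclusion.** The point holds in a limited form. The hypothesis is explained at agent level, the data are repeated within child, and the named main effect of consensus and its interaction with age do not separate the two sources of association. With no within-child relation and agent in the model, the chance of a false positive at nominal 5% is about 20–25% at 75–100 children if rho is −0.5 and about 11–12% if it is −0.3. There is no inflation at rho 0. At −0.5 it rises to 82–87% for 600 pooled children. These sizes rest on the assumed answer rates, trait SD and rho, and on four complete blocks per child. The effect on the age interaction follows from the same argument but was not sized. The documents do not show that the analysis will be pooled, that agent will be left out, or that the between-child reading is wrong. The change is worth making because the remedy is specific and cheap.

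**What to change.** In the Planned analyses of the Justifications task, reword the consensus test so that:

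- agent, agent-by-age and consensus are in one model for source naming, with the repeated blocks of a child accounted for;
- consensus is split into the child's mean over the blocks answered and the deviation from that mean, each with its age interaction;
- the agent-level hypothesis and its strengthening with age are tested on the deviation term and its interaction with age;
- the child-mean term is reported alongside as the between-child association.

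The cost is the wording of one planned analysis and one derived variable, with no new data. Under the assumed rates roughly 45% of children give the same consensus answer for every agent and add nothing to the deviation term, as does a child with only one block. Its standard error is about 15% larger than that of the undivided term. Conditional logistic regression stratified by child would also isolate the within-child relation, but it further drops children whose source answers do not vary, leaving roughly 40% informative. The centred model is therefore preferable.

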#### Child as Transmission Agent task: Open-ended storytelling about what information (religious and otherwise) is critical for a newcomer to the family

The Child as Transmission Agent task is a qualitative, exploratory task designed to capture the ways in which children are themselves vectors of information transmission, religious and otherwise. This task is part of the Child Protocol; see Fig 2.

*Task design and procedure*. In the Child as Transmission Agent task, children are asked to imagine a child who is new to their neighborhood and wants to learn how to do things the right way.

The task is divided into two blocks: The first is focused on how to behave during a religious holiday, and the second is focused on how to behave in a home setting. These blocks are presented at different points in the Child Protocol; see Fig 2.

In each block, the task is introduced with the following script: “Let’s imagine [character] is a new kid in your neighborhood who is younger than you who doesn’t know what happens at your house.” The gender of the character is matched to the gender of the participating child; if the participating child does not identify as a boy or a girl, or if the participating child’s gender is unknown, the child is shown the “girl” version of the task. The character is referred to with a common name not associated with a particular religion in the local setting.

In the *religious holiday* block, children are then told, “Now let’s say it’s a special day like [religious holiday]. [Character] needs your help to remember what you do when celebrating this special holiday.”

Children are then invited to provide open-ended instructions and explanations about the things that the character should do to observe the religious holiday the right way. These open-ended instructions are structured around two key rituals, practices, rules, or norms associated with that religious holiday; see Table 6 for items selected for each US sample. The researcher prompts the child to explain why the character should behave this way by asking, “Why should [character] do that?”

**Table 6 pone.0292755.t006:** Sample-specific item selection for the Child as Transmission Agent task, for the five religions included in US samples.

	Religion				
	*Protestantism*	*Catholicism*	*Church of Jesus Christ of L*.*D*.*S*.	*Judaism*	*Islam*
** *Both blocks* **					
*Character*	Taylor	Taylor	Taylor	Sam	Maya/Sami
*Target religious group*	Christian	Catholic	a member of the Church of Jesus Christ	Jewish	Muslim
** *Religious Holiday Block* **					
*Holiday*	Easter	Easter	Easter	Passover	Ramadan
*Item #1*	Is there anything Taylor should do or not do in the weeks before Easter?	Is there anything Taylor should do or not do in the weeks before Easter?	Is there anything Taylor should do or not do in the weeks before Easter?	What should Sam do for Passover seder (the special dinner at the beginning of Passover)?	What should Maya/Sami do if [she/he]’s invited for iftar?
*Item #2*	What should Taylor do on Easter Sunday?	What should Taylor do on Easter Sunday?	What should Taylor do on Easter Sunday?	What should Sam eat during the week of Passover?	What should Maya/Sami do if s/he comes over on Eid?
** *Home Block* **					
*Item #1*	What should Taylor do when [she/he] sits down at the table for dinner before eating?	What should Taylor do when [she/he] sits down at the table for dinner before eating?	What should Taylor do when [she/he] sits down at the table for dinner before eating?	What should Sam do when [she/he] gathers with other people for a meal?	What should Maya/Sami do after dinner before bedtime?
*Item #2*	What should Taylor do if [she/he] comes over on a Sunday?	What should Taylor do if [she/he] comes over on a Sunday?	What should Taylor do if [she/he] comes over on a Sunday?	What should Sam do if [she/he] comes over on a Friday evening?	What should Maya/Sami do if [she/he] came over on a Friday?

Unaffiliated children in the US are shown the version of the protocol that corresponds to the religion with which they are likely most familiar (see main text for details). See main text for descriptions of network-wide guidelines for item selection. “L.D.S.” stands for “Latter-day Saints.”

Next, the researcher asks, “Is there anything else you would tell [character] so she/he knows everything she/he needs to know to do things the right way when celebrating [religious holiday]?” This question is designed to elicit spontaneous references to religious practices or beliefs when transmitting information to a naive peer.

Lastly, the researcher asks, “If [character] has more questions about what to do when celebrating [religious holiday], what should she/he do?” This question is designed to elicit the salience of various information sources relevant to religion.

The *home* block follows a parallel structure. After the standard introduction to the task, children are told: “Let’s say [character] was going to come inside your house for the first time. [Character] needs your help to figure out how to do things the right way when she/he comes over.” Children are then invited to provide open-ended instructions and explanations about the things that the character should or shouldn’t do when visiting the participating child’s home for the first time, structured around two moments in an ordinary day that might be associated with religious ritual (e.g., what to do or not do when entering the house, meeting an adult, or preparing for dinner). As in the *religious holiday* block, children are then invited to offer the character additional tips and to suggest sources of additional information.

At the end of each block, children are asked whether the character is a member of the target religious group or not. Depending on the sampling plans in place at a given field site, the target religious group featured in this task might correspond to the participating child’s own religious group membership, to a religious group with which the child’s parent has indicated that they are familiar, or to a religious group that is prevalent in the participating child’s local context. The target religious group featured in this task is matched to the religious “target group” or “reference group” featured in the Sorting, Religious Indicators, Social Essentialism, and Norm Violations tasks (described in other sections).

In the US samples, each block is estimated to take 2 to 5 minutes across the age range, for a total of 4 to 10 minutes for the task as a whole.

*Adaptation for US samples*. The final set of properties featured in the Child as Transmission Agent task for the five religions included in US samples is presented in Table 6.

*Parallel tasks with parents/caregivers*. There is no parallel task for parents/caregivers.

*Planned analyses*. Before describing our analysis plans, we again note that analyses of the many open-ended questions included in this task will require the development of coding schemes to note the presence and extent of various kinds of content (e.g., identifying certain content as “religious”; counting mentions of “God” or other religious agents; coding different types of explanations for why the character should or should not behave in a certain ways, as well as various manners of speaking (e.g., noting the use of generic sentences). These coding schemes have not yet been developed.

We hypothesize that older children will be more likely to spontaneously mention religious rules, practices, rituals and other religious content than younger children, and will offer richer and more detailed examples, descriptions, and explanations of this religious content [see 71, 72]. To test these hypotheses, we will examine the main effects of participant age (4–10 years) using any relevant coding schemes we have developed to quantify and characterize religious content in children’s responses.

We also anticipate comparing responses in the two blocks of this task via examinations of the main effects of setting type (religious holiday vs. home) as well as statistical interactions between setting type and participant age.

Beyond these predictions, we plan to conduct item-level analyses (e.g., examining differences across questions about the two specific “moments” in the home); to compare responses across samples from different cultural-religious groups; to explore relationships between children’s responses in this task and information provided in the Parent Survey; and to examine relationships between this and other tasks included in the Child Protocol.

